### Outcomes

Primary outcomes will be collected at baseline and weekly over a period of 6 months of intervention through an online, self-reported electronic questionnaire, created by the research team. The physical activity intervention group will receive a reminder every week through the web app with a brief questionnaire related to the primary outcomes. The standard care group will receive a SMS reminder every week with a link to the same questionnaire. Secondary outcomes will also be collected electronically at baseline, 6 and 12 months. Both groups will fill out the same questionnaire through the same system. The electronic version of the baseline questionnaires and the weekly questionnaire were created by the research group and will be hosted by the University of Sydney.

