#### Inclusion criteria

Adults over 18 years of age with chronic LBP persisting for over 12 weeks but without radicular symptoms; who have been discharged from a hospital-based, LBP physiotherapy program but still have consistent pain (at least 3 in the Numerical Rating Scale); with regular (weekly) use of a computer or internet-connected mobile/tablet device; and fluency in English (verbal and written).

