*The IMPACT web app:* The IMPACT web app: A mobile web app will be built and hosted by the University of Sydney. The app will be customised specifically for the purposes of this project to allow participants to monitor their goals and their physical activities. Participants will be able to access the app at any time and write reports about their physical activity related goals to their health coach as well as receive coach-tailored feedback. In addition, each participant will receive a quick questionnaire every week to monitor their pain levels, based on the Numerical Rating Scale; disability, based on the Rolland-Morris disability questionnaire and care-seeking associated with LBP. This questionnaire was created specifically to this project. The health coach will have the ability to view the participant’s report and communicate with them by phone fortnightly to discuss their goals and update them according to their reports and feedback. Personalised messages constructed by the health coach will be sent every week to encourage participants to achieve their goals. In summary, the IMPACT web app will be designed to facilitate monitoring achievement and providing updates on participants’ goals, encouraging them to engage in physical activity and track potential adverse events.

*The standard care control group* will receive the ‘*Make your move – Sit less, be active for life!’* booklet and will be advised to work towards increasing their physical activity levels and achieving their two long-term goals as defined at baseline.

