### Ethics

The trial includes key methodological features to minimise bias in controlled trials: randomisation, concealed allocation, specification of eligibility criteria, blinded outcome assessment, blinded analysis, and intention-to-treat analysis. Data will be stored in spreadsheets and transferred to appropriate statistical software for analysis by an investigator blinded to group allocation. Spreadsheets will be regularly scrutinised for omissions and errors. Data will be stored and accessed as per the University of Sydney ethics requirements.

This protocol was registered at the Australian New Zealand Clinical Trials Registry (ACTRN12615000189527) and was prospectively approved by the Human Research Ethics Committee from the South Western Sydney Local Health District (Local HREC reference 15/015).

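### The primary outcomes are self-reported by participants who will know their arm, so blinded outcome assessment does not hold for them, and the weekly reminder route differs by arm

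*Protocol article*

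**What the plan says.** The Outcomes section states how the primary outcomes are obtained: "Primary outcomes will be collected at baseline and weekly over a period of 6 months of intervention through an online, self-reported electronic questionnaire". The Primary outcomes subsections confirm that care-seeking, the pain rating (NRS) and the Roland–Morris score (RDQ) are all gathered this way each week.

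The prompts are described separately by arm. For the intervention arm: "The physical activity intervention group will receive a reminder every week through the web app with a brief questionnaire related to the primary outcomes". For controls: "The standard care group will receive a SMS reminder every week with a link to the same questionnaire". After a sentence on secondary outcomes, the same section adds: "Both groups will fill out the same questionnaire through the same system".

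The Interventions section, under the IMPACT web app, presents the weekly questionnaire as part of the app: "each participant will receive a quick questionnaire every week to monitor their pain levels". The same paragraph lets the health coach view the participant's report and gives the app a role in tracking possible adverse events.

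On blinding, Study design calls the trial single-blinded without saying who is blinded. Procedures describes a blinded research assistant who extracts data. Statistical analysis promises blinded analysis. Ethics lists among the trial's safeguards "blinded outcome assessment, blinded analysis, and intention-to-treat analysis".

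**The concern.** For a self-rated outcome the participant is the assessor. If participants know their arm, blinded data handling further down the line does not make the assessment blind. A reader who takes the Ethics statement at face value would credit the trial with protection that none of its primary outcomes has.

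The second issue is avoidable. Participant knowledge of the arm comes with any comparison of coaching and a booklet, but prompting one arm through the intervention itself is a choice. An intervention participant who loses interest in the app also loses the outcome prompt; a control participant's prompt does not depend on engagement with anything. Response, and possibly the answers, could then differ by arm for reasons other than back pain. The pilot is meant to inform the effect size and design of a larger trial, so an arm-dependent collection route could be carried forward.

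**Working it through.** No figure in the article bears directly on this point, so the first check sets the passages side by side.

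1. **Who assesses?** The participant does, for all three primary outcomes (Outcomes; Primary outcomes).
2. **Can the participant be blind?** The article does not say. The intervention arm receives a home coaching session, 12 telephone calls, a Fitbit, the app and the booklet; controls receive the booklet only (Abstract; Interventions). Knowledge of the arm follows from this.
3. **What is blinded?** Data extraction, described with the accelerometer procedures (Procedures), and the analysis (Statistical analysis; Ethics). Neither blinds a self-rated score.
4. **What is claimed?** Blinded outcome assessment, without restriction (Ethics). Steps 1 to 3 contradict this for every primary outcome.
5. **What is the same in both arms, and what differs?** The questionnaire is the same. The system is stated to be the same, although that sentence follows the one on secondary outcomes, so its scope is unclear. The reminder and access route differ: web app against SMS link.
6. **Does the coach see outcome answers?** Unclear. The app paragraph speaks first of reports on goals, then of the weekly questionnaire, then of the coach viewing the participant's report.

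The following only illustrates what could be at stake. The standard deviation (1.9), the 2-point target, 34 per arm and the 35% maximum loss come from Sample size calculation. The bias values, the loss by arm and the gap between missing and responding patients are assumptions.

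*Reporting shift.* A two-sided 5% t-test with no true effect and a shift b between arms has noncentrality b / (1.9 × √(2/n)). With 35% loss, n = 34 × 0.65 = 22.1, so about 22. For b = 0.5 and n = 22: 0.5 / (1.9 × √(2/22)) = 0.5 / 0.573 = 0.87.

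| Assumed shift (NRS points) | Rejection rate, 22 per arm | Rejection rate, 34 per arm |
|---|---|---|
| 0 | 5% | 5% |
| 0.25 | 7% | 8% |
| 0.5 | 14% | 19% |
| 0.75 | 25% | 36% |
| 1.0 | 40% | 57% |

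*Unequal response, responder-only comparison.* Full-arm mean = responder mean + loss × gap, so the between-arm shift is (difference in loss) × gap. All three splits below average 35%; the assumed gap is 1 to 2 points.

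- 35% v 35%: 0 × gap = 0
- 25% v 45%: 0.20 × gap = 0.2 to 0.4 points (10% to 20% of the 2-point target)
- 20% v 50%: 0.30 × gap = 0.3 to 0.6 points

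These are not the bias of the planned mixed model. Unequal response costs little power: 22 v 22 completers give about 93% for a 2-point difference, and 27 v 17 about 91%. The issue is bias, not precision.

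**The case against.** The strongest reply is that unblinded self-report is inherent in a trial of coaching against a booklet. The article calls itself single-blinded, never says that participants are blinded, and describes blinded extraction and analysis that are achievable. That is fair. It makes the first part a correction of one statement, not a design failure, but the statement is still wrong for the primary outcomes.

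Four stronger readings are tempting, and the article does not support them.

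- *The arms report through different channels.* The article says "Both groups will fill out the same questionnaire through the same system". Even with its scope in doubt, what is shown to differ is the reminder and access route.
- *The coach reads the pain scores.* The report that the coach views may well be the goal report. The text is ambiguous, and access rights may be set out in the full protocol.
- *SMS will miss some controls.* Eligibility requires "regular (weekly) use of a computer or internet-connected mobile/tablet device". This sets a minimum of internet use; it does not suggest that anyone lacks a mobile phone.
- *With 35% loss, the result is biased by 0.2 to 0.4 points.* The 35% is a maximum loss to follow-up, not an expected rate of questionnaire non-response, and no split by arm is given. Different response rates alone do not bias the estimate. The planned linear mixed model uses every observed week and is valid if data are missing at random; bias from missing data needs missingness that depends on unobserved outcomes.

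The mixed model does not, however, correct a shift in how participants rate themselves.

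**Conclusion.** The point holds in two parts. First, the claim of blinded outcome assessment is wrong as written for all three primary outcomes. This rests on the inference, which the interventions make hard to avoid, that participants know their arm. Second, the weekly prompt runs through the intervention app in one arm and by SMS in the other, so completion in the intervention arm may depend on engagement with the intervention. That is a risk; nothing in the article shows that response will differ.

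The size of any bias cannot be derived from the document. The figures above show sensitivity under assumed values and a simple comparison, and should not be read as estimates for the planned analysis.

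**What to change.** 1. In Ethics, replace the claim of blinded outcome assessment with wording such as: *primary outcomes are self-reported by unblinded participants; data extraction and statistical analysis are blinded*. Limit the conclusions accordingly.
2. Send the weekly reminder and questionnaire link to both arms by the same route. The SMS link already used for controls would serve.
3. State that the coach cannot see the primary-outcome answers, and keep the app's adverse-event tracking by a separate path.
4. Compare weekly completion by arm.

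The first change costs one sentence. The others cost a second prompt outside the app for the intervention arm and a separate adverse-event item. None of this removes the bias that unblinded self-report can bring; it removes the avoidable asymmetry and describes the rest correctly.

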#### Primary outcomes

##### Care-seeking associated with LBP

*C*are-seeking will be assessed at baseline and weekly over a 6- month period through a specifically designed electronic questionnaire. The participant will be able to register information related to care-seeking such as any visits to a health practitioner (i.e. general practitioner, physiotherapist, chiropractor, etc), type of pain self-management (i.e. heat pack, bed rest, hot shower, etc), and medication intake (i.e. type of medication taken).

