### Recruitment method

Treating physiotherapists will screen (all) potential participants from the outpatient Physiotherapy Department of the Liverpool Hospital, South Western Sydney Local Health District, Australia, and inform them about the study. Potential participants interested in participating in the study will receive the Participant Information Statement and be referred to the research team. Patients with chronic LBP who have received any conservative physiotherapy treatment (e.g. exercises, spinal manipulative therapy) and meet the inclusion criteria will be invited to participate in the trial after treatment discharge. At treatment discharge, a research assistant will discuss the study and offer participation to those who meet the inclusion criteria. If they agree to participate a signed consent form will be recorded and baseline data will be collected.

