### Group allocation

Random allocation to physical activity or standard care groups will occur after confirmation of eligibility and baseline assessment. Allocation will be blinded and performed using a computer-generated random allocation schedule operated by a remote researcher. The allocation of participants will be concealed by using sequentially numbered, sealed and opaque envelopes.

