### Procedures

Patients attending outpatient physiotherapy will be screened by their treating physiotherapists, who will determine eligibility, inform about the trial objectives and invite participation. The ones that manifest interest will be given the Participant Information Statement by their treating physiotherapist and decide if they want to participate in the study. A senior physiotherapist from Liverpool Hospital will be responsible for booking potential participants on their second to last appointment to meet the investigator after discharge. At discharge, patients that agree to participate will be asked to sign the consent form. The assessor will collect demographic and anthropometric data (age, height, weight, waist circumference) as well as baseline data related to the study outcomes. A device able to accurately estimate how physically active a person is throughout the day (*Actigraph*) by measuring 3-dimensional body accelerations will be given to all participants at baseline with clear instructions for use and telephone support available. The *Actigraph* will collect accelerometer-based data over a 1-week period to account for day-to-day variation in physical activity levels [23]. Participants will be provided with pre-paid envelopes to return the devices to the research centres. The *Actigraph* has been successfully used to measure physical activity in large-scale population-based studies internationally [23, 24]. The analyses will be adjusted for accelerometer wear time defined by ‘off time’. Any period of greater than 60 min with no activity at all will be considered to be ‘off time’ and excluded from the analyses. Data will be extracted by a research assistant who will remain blinded to group assignment throughout the trial.

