### Statistical analysis

The effect of treatment will be separately analysed for each outcome using linear mixed models with time as a repeated factor, group as a fixed factor and participants as a random factor. The coefficient of the group x time interactions will provide estimates of the effects of interventions over time. Between-group differences in mobility-related goal attainment, at 6 months after randomisation, will be analysed with ordinal regression. To aid interpretation of goal attainment, the scores will also be dichotomised (goal met versus goal not met), and odds ratios calculated. Accelerometer data will be processed using ActiLife 6 software. Acceptable wear time will be set a priori and defined as 4 days or more of 10 h or more per day. All analyses will be performed by intention-to-treat and blinded to treatment group. Potential covariates that will be investigated are baseline pain and disability levels, number of previous treatments, symptom duration, co-morbidities, age and socioeconomic status.

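### Reading the care-seeking effect as group x time against a baseline taken at discharge from physiotherapy contrasts follow-up with care under treatment and loses precision; a post-randomisation comparison avoids both

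*Protocol article*

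**What the plan says.** All references are to the protocol article.

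- **Inclusion criteria.** Participants are people "who have been discharged from a hospital-based, LBP physiotherapy program but still have consistent pain".
- **Recruitment method.** "At treatment discharge, a research assistant will discuss the study and offer participation to those who meet the inclusion criteria". Then: "If they agree to participate a signed consent form will be recorded and baseline data will be collected".
- **Procedures.** The assessor collects demographic and body measurements "as well as baseline data related to the study outcomes".
- **Group allocation.** "Random allocation to physical activity or standard care groups will occur after confirmation of eligibility and baseline assessment".
- **Care-seeking associated with LBP.** The initial C falls outside the quote: "are-seeking will be assessed at baseline and weekly over a 6- month period through a specifically designed electronic questionnaire". The questionnaire registers "any visits to a health practitioner (i.e. general practitioner, physiotherapist, chiropractor, etc", and also types of self-management and medication. Visits belonging to the qualifying programme are not excluded.
- **Statistical analysis.** Each outcome gets a linear mixed model in which time is a repeated factor, except that goal attainment is analysed by ordinal regression. "The coefficient of the group x time interactions will provide estimates of the effects of interventions over time". Baseline pain and disability are listed as possible covariates; baseline care-seeking is not.

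**The concern.** One model template is used for all three primary outcomes. It suits pain and disability, whose values at discharge mean the same as their values later. It does not suit care-seeking. At discharge every participant has just been attending a physiotherapist because of the entry criterion. A baseline item that looks back far enough to reach the last appointments records how the hospital spaced them. If the form leaves those appointments out, the value is still care-seeking while under treatment. Neither is the quantity the trial wants to compare, which is care sought after discharge.

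The stake is precision on a primary outcome in a trial of 68. The article also says its findings will inform the effect size and design of a larger trial, so a needlessly noisy estimate would carry forward.

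**Working it through.** The article gives no figure for care-seeking; its sample size rests on pain. There is therefore nothing of its own to reproduce, and every visit rate below is an assumption.

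**Inputs**
- From the article: 34 per arm, maximum loss 35%, so 34 x 0.65 = 22.1, taken as n = 22 per arm; 26 weekly reports over 6 months.
- Assumed: mean m of 0.1 to 0.4 visits per week after discharge, with gamma variation between people (shape k of 0.5 to 2) and Poisson counts.
- Assumed: one programme visit in the baseline week, plus a second with probability p of 0.1 to 0.5, unrelated to later visits.
- Central case: m = 0.2, k = 1, p = 0.3.

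**Formulas** (variance per person; with complete data the average of the 26 interaction terms is the between-arm difference in change from baseline)
- Direct follow-up comparison: V1 = m²/k + m/26
- Change from a baseline containing programme visits: V2 = V1 + p(1 − p)
- Change from a clean one-week baseline at the person's own rate: V3 = m + m/26, because the personal rate cancels
- SE of the between-arm difference = √(2V/n). Ratios of SEs do not depend on n.

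**Central case**
- V1 = 0.04 + 0.0077 = 0.0477; SE = √(2 x 0.0477/22) = 0.066
- V2 = 0.0477 + 0.21 = 0.2577; SE = 0.153; ratio to direct = 2.3
- V3 = 0.2 + 0.0077 = 0.2077; SE = 0.137; ratio to direct = 2.1
- Part due to programme visits: 0.153/0.137 = 1.11, or about 11%
- Information lost: 1 − 0.0477/0.2577 = 81% with programme visits; 1 − 0.0477/0.2077 = 77% with a clean baseline

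**Across the assumed range**
- Smallest ratio to direct (m = 0.4, k = 0.5, p = 0.1): V1 = 0.3354, V2 = 0.4254, ratio 1.13
- Largest (m = 0.1, k = 2, p = 0.5): V1 = 0.0088, V2 = 0.2588, ratio 5.4
- Programme baseline against clean baseline, lowest (m = 0.4, k = 2, p = 0.1): √(0.1854/0.4154) = 0.67
- Programme baseline against clean baseline, highest (m = 0.1, k = 0.5, p = 0.5): √(0.2738/0.1038) = 1.62

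The programme can thus raise or lower the SE, because one or two scheduled visits can vary less than a person's own sparse weekly count.

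**Second check, different assumptions.** This simulation used 34 per arm, k = 2, true follow-up rates of 0.1 and 0.2 per week (difference −0.10), and Poisson programme visits averaging 0, 0.5, 1 or 2.
- Estimated difference in change: −0.101, −0.102, −0.100, −0.097. There is no bias.
- SE of that difference: 0.11, 0.20, 0.27, 0.36, against 0.033 for follow-up only.

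Even with no programme visits the SE is about 3.4 times the direct one (0.1117/0.0329). The programme's own share is larger here than 11% because Poisson visits were assumed to be more dispersed.

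**The case against.** The strongest reply is that the precision loss is mostly not caused by the programme. That is right: in the central case the ratio is already 2.1 with a clean baseline week, and across the assumed range the programme can lower the SE as well as raise it. The cost comes mainly from contrasting 26 weeks of follow-up with one sparse week. The fix is the same either way.

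Other parts of the reply also stand:

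- The baseline look-back, the item wording and the scoring are not given. The Outcomes section mentions baseline questionnaires separately from the weekly one, and the Procedures section has participants meeting the investigator after discharge, with no interval stated. A reader might infer that baseline certainly scores the programme; the article does not establish that.
- The article does not name baseline as the reference level. This is inferred from its being collected with the weekly values and from time being a repeated factor. The exact model could be settled in an analysis plan that is not shown.
- Visits are one component. Self-management and medication are not scored automatically by attending physiotherapy.
- If visits were scored only as any or none, a baseline that captured the programme would be constant and would cost no precision.

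A reader might also infer that the trial would mistake a fall from baseline in both arms for a reduction in care-seeking. The plan does not support this: no within-arm test is specified, and a common fall cancels in group x time.

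The reply does not remove the mismatch. Even if the form excludes programme visits, the baseline still describes the period under treatment, and the stated effect measure gives that value a role it does not need.

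**Conclusion.** The point holds in a limited form. As the article most naturally reads, the care-seeking effect is a change from a value taken at the end of treatment, which is not the post-discharge quantity and makes a poor reference. It does not bias the between-arm estimate: baseline precedes randomisation and both arms share the same entry condition. The harm is to precision. The SE is about 1.1 to 5.4 times that of a direct follow-up comparison, 2.3 in the central case. Of that, 2.1 would arise with any single clean baseline week, and about 11% is added by programme visits.

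These sizes rest on assumed visit rates, on visits being counted, on a one-week baseline look-back, and on baseline being a level of the time factor. They apply to the visit component only. It would overstate the case to attribute the whole loss to programme visits or to call the treatment effect biased.

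**What to change.** For care-seeking only, define the effect as the between-arm difference over post-randomisation weeks 1 to 26, in place of group x time against baseline. On the baseline form, state the look-back and ask for LBP care outside the qualifying physiotherapy programme; use that value only as a covariate or descriptor. The model for pain and disability need not change on this account.

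Cost: one sentence in the analysis section and one instruction on the baseline form. No extra participants or visits are needed.
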